## Abstract

**Background:**

Incremental haemodialysis/haemodiafiltration (HD) may help reduce early mortality rates in patients starting HD. This mixed-method feasibility study aims to test the acceptability, tolerance and safety of a novel incremental HD regime, and to study its impact on parameters of patient wellbeing.

**Method:**

We aim to enrol 20 patients who will commence HD twice-weekly with progressive increases in duration and frequency, achieving conventional treatment times over 15 weeks (incremental group). Participants will be followed-up for 6 months and will undergo regular tests including urine collections, bio-impedance analyses and quality-of-life questionnaires. Semi-structured interviews will be conducted to explore patients’ prior expectations from HD, their motivations for participation and experiences of receiving incremental HD. For comparison of safety and indicators of dialysis adequacy, a cohort of 40 matched patients who previously received conventional HD will be constructed from local dialysis records (historical controls).

**Results:**

Data will be recorded on the numbers screened and proportions consented and completing the study (primary outcome). Incremental and conventional groups will be compared in terms of differences in blood pressure control, interdialytic weight changes, indicators of dialysis adequacy and differences in adverse and serious adverse events. In analyses restricted to incremental group, measurements of RRF, fluid load and quality-of-life during follow-up will be compared with baseline values. From patient interviews, a narrative description of key themes along with anonymised quotes will be presented.

**Conclusion:**

Results from this study will address a significant knowledge gap in the prescription HD therapy and inform the development novel future therapy regimens.

**Supplementary Information:**

The online version contains supplementary material available at 10.1007/s10157-021-02072-1.

## Introduction

In patients with advanced chronic kidney disease (CKD), the start of haemodialysis/haemodiafiltration (HD) therapy marks the start of a critical transitional period. The abrupt changes in patients’ lifestyles, independence and work [1, 2] combined with the additional burden of pathophysiological changes with the onset of regular dialysis [3–5] worsening indices of nutrition and inflammation with advancing CKD [6, 7] an increasing burden of co-morbid illnesses [8] and a decline in functional status especially in the elderly [9], can all lead to higher risk of decompensation in the early days of therapy [10, 11]. Mortality rates are highest in the first few weeks of treatment [12–14].

Incremental HD, which enables patients to start dialysis with smaller doses and gradually building up to traditional full dialysis over a longer period, may help reduce some of the associated risks early on by allowing patients the time to adapt physically and mentally to the new changes [15, 16]. Ultimately, a randomised control trial (RCT), testing incremental HD vs. standard care will be needed to definitively address if starting HD incrementally reduces mortality in incident dialysis starters [17, 18]. Key uncertainties need to be addressed, however, before a definitive RCT can be conducted:A.Wide variations exist in the practice of incremental HD worldwide [19, 20]. The optimal design for a suitable regimen that is safe, effective and easy to administer needs to be fully established through feasibility testing before it can be formally tested in an RCT.B.The level of patient interest and demand for incremental HD require further exploration. This information is needed for planning of resources in the future RCT.C.The most suitable *primary* outcome measure for use in a future RCT needs further study (this information is needed for the sample size calculation)D.Given the time constraints that come with the delivery of each dialysis session and the already high frequency of patient exposure to healthcare environment, which additional tests should be included in the future RCT to help fully understand the impact of incremental HD on patient’s health.

To pave the way for a future RCT of incremental HD vs standard care, a feasibility study is being conducted which aims to establish the acceptability, tolerance and safety of a novel incremental HD regime; and to explore the feasibility of data collection and follow-up of the participants.

## Materials and methods

### Study design

A mixed-method study with two key elements:A prospective interventional study, with historical matched controls, involving new HD starters; testing the feasibility and safety of incremental HD and examining the impact of incremental HD on patients’ wellbeing (the ‘interventional cohort study’).Semi-structured interviews of study participants to document and analyse the experiences of patients receiving incremental HD (the ‘interview phase’).

### Settings

A large University Teaching Hospital in the UK (Hull University Teaching Hospitals NHS Trust) and its three associated satellite dialysis units [21].

### Participants

Adults with CKD stage 5 (from any cause), commencing in-centre maintenance HD therapy for end-stage renal disease (ESRD) in the out-patient settings. Full eligibility and exclusion criteria are presented in Table 1. Pre-dialysis specialist nephrology input for at least 3 months is essential since those without full preparation for dialysis may require intensive dialysis at presentation [22, 23] (i.e., unsuitable for incremental HD).

**Table 1 Tab1:** Eligibility criteria for study participants

Inclusion criteria	Exclusion criteria
Age ≥ 18 patients with CKD-5 who are about to start planned HD At least 3 months of prior specialist renal follow-up at the time of starting HD Able to meet all the study requirements Written signed informed consent	Age < 18 No prior contact with nephrologists for > 3 months Cross-over into HD from peritoneal dialysis Currently undergoing HD therapy Any condition which in the opinion of the investigator makes the participant unsuitable for entry into the study Participation in an interventional study in the preceding 6 weeks History of myocardial infarction in the preceding 3 months Inability to provide informed consent Inability to comply with the study schedule and follow-up

*CKD* chronic kidney disease, *HD* haemodialysis

### Recruitment

#### Recruitment for the intervention arm

Participants will be approached at the specialist pre-dialysis clinics or the dialysis unit with the participant information sheet (PIS). They will be given at least 24 h to consider the information. Following this, the investigator will meet patients in person to address their questions and obtain written informed consent if they show willingness to proceed. They will remain in-active in the study, and under follow-up with their usual care providers, until the decision is made to start HD by their caring physician. The timing of HD initiation will be made independently of the study investigators by the clinical care teams, based on clinical needs and in consultation with patients and their relatives. Clinicians will not be blind to patients’ participation in the study; some pre-dialysis CKD-5 patients may have already signed up for the study prior to commencing dialysis. Whether the knowledge of patients’ interest in incremental HD influences decisions about the timing of starting HD is not known. The starting eGFRs will be reported for both incremental and control arm patients which could help address this current knowledge gap.

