#### Recruitment for control arm (historical controls)

Each participant in the incremental HD arm of the study will be matched with 2 patients who had previously received the conventional HD treatment (historical controls; matching ratio 1:2). Participants for the control arm will be identified using the local dialysis treatment database. All patients starting HD therapy since 2013, the inception date of the database, will be included in the searches. Their dialysis treatment data (including nursing notes and exceptions), along with details of their medical history will be extracted for further analysis (see below).

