#### Matching method

Propensity scores matching (PSM) will be undertaken to match participants in the incremental HD group with controls. Propensity scores will first be computed using logistic regression analysis accounting for the following 14 variables: age, C-reactive protein (CRP), serum albumin, vascular access type, pre-dialysis serum creatinine, dialysis facility, body mass index (BMI), parathyroid hormone levels (PTH), diastolic blood pressure (BP), haemoglobin, systolic BP, vitamin K antagonist treatment, history of cardiovascular disease and antihypertensive treatment. These variables together predict 2-year mortality in new dialysis starters with sensitivity and specificity of 72% and 69% based on a study by Siga et al. [24]. Matching will take place using the nearest neighbour method (no pre-specified caliper range) with no replacements.

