### Sample size

As this is a feasibility study, a formal sample size calculation has not been performed. The recruitment target is 20 participants in the active interventional arm and 40 in the historical control group (1:2 matching).

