### Measurements and data items

#### Baseline data

Data items recorded at baseline include age, gender, primary renal disease, names of co-morbid conditions, medications list (including the names of anti-hypertensives and diuretics), date of first contact with nephrology services, type of vascular access and estimated glomerular filtration rate (eGFR) based on serum creatinine measurement prior to first dialysis session. Charlson co-morbidity index [25] will be calculated for all participants to enable baseline comparison of the burden of co-morbidities. With patients’ permission, we will cross-reference medication lists with their primary care records to ensure completion.

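### Starting eGFR is to be compared between arms to study the timing of HD start, but the controls are matched on creatinine and age, which biases that comparison strongly towards no difference

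*Protocol article*

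**What the plan says.** Four statements in the protocol article bear on this.

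- **The question.** Recruitment for the intervention arm says that clinicians are not blind to participation, and then: "Whether the knowledge of patients’ interest in incremental HD influences decisions about the timing of starting HD is not known".
- **The proposed evidence.** The next sentence of that section reads: "The starting eGFRs will be reported for both incremental and control arm patients which could help address this current knowledge gap".
- **How starting eGFR is obtained.** Baseline data lists "estimated glomerular filtration rate (eGFR) based on serum creatinine measurement prior to first dialysis session".
- **How the control arm is chosen.** Under Recruitment for control arm, "Each participant in the incremental HD arm of the study will be matched with 2 patients who had previously received the conventional HD treatment", drawn from all HD starters in the local database since 2013. Matching method gives a logistic propensity score on 14 variables, beginning with "age, C-reactive protein (CRP), serum albumin, vascular access type, pre-dialysis serum creatinine". It then states: "Matching will take place using the nearest neighbour method (no pre-specified caliper range) with no replacements".

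The article mentions no report of eGFR from the unmatched pool.

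**The concern.** The comparison asks whether participants begin HD at a different level of kidney function from patients who began before the study existed. For that, the comparison group has to show the level at which patients used to start. The matched controls do not show this, because they are picked to resemble the participants on the main determinants of eGFR. If knowledge of the study leads to earlier starts, participants have lower creatinine, the score favours past patients who also had lower creatinine, and the gap shrinks before it is looked at.

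The study exists to prepare an RCT, and its 6-month follow-up runs from the first day of HD. A shift in starting point would affect who enters such a trial and how comparable outcomes counted from that day are. A table of similar eGFRs would look reassuring on this point when it carries little information.

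**Working it through.** **The plan's own figure.** 20 participants × 2 controls = 40, as the Sample size section states. The article gives no power or effect size for eGFR.

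**Why matching reaches eGFR.** With the creatinine-based formula assumed here, and creatinine in the range of these patients,

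log eGFR = constant − 1.209 × log(creatinine) + age × log(0.993) + sex terms.

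At a given age and sex, an eGFR 1.25 times higher means a creatinine ratio of 1.25^(−1/1.209) = 0.83. An eGFR 1.5 times higher means 1.5^(−1/1.209) = 0.72. Creatinine and age are both in the score. Sex is recorded at baseline but is not a matching variable.

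**Simulation of the planned matching.** From the article: 20 participants, 14 variables including age and creatinine, logistic score, 1:2 nearest neighbour, no caliper, no replacement. Assumed, because the article does not give them: control eGFR with median 8 mL/min and log-SD 0.33, mean age 65, 38% women, the other 12 variables as independent noise, pools of 150, 300 and 600, and a true shift that multiplies participants' eGFR by 1.25 or 1.5. There were 400 runs per scenario.

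The assumed control mean is 8 × exp(0.33²/2) = 8.45. The expected true gaps are therefore 0.25 × 8.45 = 2.11 and 0.5 × 8.45 = 4.22 mL/min.

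| Pool | Shift | Unmatched gap | Matched, creatinine in score (SD between studies) | Lost | Matched, creatinine omitted |
|---|---|---|---|---|---|
| 150 | ×1.25 | 2.10 | 0.74 (0.68) | 65% | 2.09 |
| 300 | ×1.25 | 2.14 | 0.61 (0.60) | 72% | 2.08 |
| 600 | ×1.25 | 2.21 | 0.50 (0.63) | 77% | 2.15 |
| 150 | ×1.5 | 4.15 | 1.96 (0.89) | 53% | 4.34 |
| 300 | ×1.5 | 4.26 | 1.49 (0.74) | 65% | 4.21 |
| 600 | ×1.5 | 4.20 | 1.15 (0.69) | 73% | 4.25 |

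Lost = 1 − matched/unmatched; for example 1 − 0.74/2.10 = 65%. The last column comes from separate simulated data, so small departures from the unmatched column are simulation noise. With no true shift, all the differences were within 0.1 of zero.

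Three things follow.

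1. Creatinine in the score is the cause: without it the gap survives.
2. The loss grows with the pool, because closer matches become available.
3. In a single study the ×1.25 residual is only about one between-study SD from zero (0.74/0.68 = 1.1, 0.61/0.60 = 1.0, 0.50/0.63 = 0.8). The ×1.5 residual is about two (1.96/0.89 = 2.2, 1.49/0.74 = 2.0, 1.15/0.69 = 1.7).

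Widening the assumptions to pools of 150 to 800 and true gaps of about 1.3 to 4.2 mL/min gives losses of about 50% to 85%.

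**Precision of an unmatched comparison.** The assumed spread gives an SD of about 8.45 × √(exp(0.33²) − 1) = 2.9. The 95% half-width is 1.96 × 2.9 × √(1/20 + 1/pool), which is 1.35 for a pool of 150 and 1.29 for 600.

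**The case against.** The best defence is that the article claims little. It says the eGFRs will be reported and could help. It names no test, threshold or decision, starting eGFR is not a listed outcome, and formal testing of secondary outcomes is ruled out. Participants' own starting eGFR is untouched by matching and can be set against any reference. For the safety comparisons, which are what the control arm is for, balancing creatinine is defensible. All of this stands. It limits the harm to how one descriptive comparison is read, but it does not make that comparison informative.

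A reader might go further and infer that matching abolishes any difference by construction, so that the study is bound to conclude that timing is unaffected. The documents do not support that. Matching is on a single score built from 14 variables with no caliper, so balance on creatinine is imperfect and part of a gap remains. Near-total loss did appear under one other set of assumptions, for a true gap of 1.3 mL/min with pools of 400 and 800 (residuals 0.03 and −0.08). The same set left 1.0 of a 3.0 gap with a pool of 200. The article also announces no conclusion about timing.

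Two further limits are fair. The article does not say that the creatinine used for matching and the one used for eGFR are the same sample, though both are described as pre-dialysis values. And an unmatched comparison mixes timing with case-mix and calendar period, so it improves on the matched one without settling the question.

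**Conclusion.** The point holds. Followed as written, the plan answers a question about the level at which HD is started with controls selected partly on that level. The direction of the bias follows from the article's own statements and needs no assumed figure beyond creatinine and age being inputs to eGFR. The size, roughly half to 85% of a real gap, depends on the assumed pool size, eGFR spread, covariate structure and timing shift, none of which the article gives.

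Similar eGFRs in the matched arms would be weak evidence that timing is unaffected. A gap that remains would be hard to interpret too, since it could reflect imperfect matching or the unmatched sex term. The recruitment and retention outcomes are not affected, and this point is no argument against matching on creatinine for the safety comparisons.

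**What to change.** Separate the two uses of the historical data.

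- **Timing question.** Compare participants' starting eGFR descriptively, as a mean difference with 95% CI, with all historical starters since 2013 who meet those Table 1 criteria that can be checked in records. Leave them unmatched and adjust for calendar year and basic case-mix other than creatinine. A second match that omits creatinine from the score is an acceptable alternative.
- **Safety comparisons.** Keep the current matched set, and label the eGFRs reported for it as a check of balance, not as evidence on timing.

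State the limits beside the result: remaining selection and calendar differences, and an interval of about ±1.3 mL/min under the assumed spread, so a gap of that size would barely be distinguishable from zero.

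The cost is modest. Fitting the score already requires creatinine and age for the whole pool, and no new visits or tests are needed. The added work is record checking for planned start, 3 months of prior nephrology follow-up, transfer from peritoneal dialysis and recent myocardial infarction, which the article does not show as already applied to the pool.

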#### Recruitment for control arm (historical controls)

Each participant in the incremental HD arm of the study will be matched with 2 patients who had previously received the conventional HD treatment (historical controls; matching ratio 1:2). Participants for the control arm will be identified using the local dialysis treatment database. All patients starting HD therapy since 2013, the inception date of the database, will be included in the searches. Their dialysis treatment data (including nursing notes and exceptions), along with details of their medical history will be extracted for further analysis (see below).

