### Study timeline and future plans

Final analyses will be completed after the 20th participant (or the last participant recruited within the 18-month recruitment period) has completed 6 months follow-up (September 2021). Data obtained from this feasibility study will be used to design the incremental HD regime to be used in a future RCT.

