As above, we have also bypassed the need for timed urine collections in the follow-up period by introducing monitoring measures that focus on key safety parameters (i.e. additional tests for hyperkalaemia and hydration status). This approach opens incremental HD to a wider section of new dialysis starters, particularly to the elderly. We pre-specify fixed increments in HD treatment times, providing more certainty to patients and helping dialysis staff with the planning of treatments.

The use historical controls is novel in dialysis research. A control arm is needed to compare the rates of pre-defined safety events, and to study the impact of incremental HD on selected patient outcomes. The delivery of modern HD therapy is highly regimented and treatment records are readily accessible through dedicated dialysis databases. This makes the use of historical controls a feasible option, particularly when examining rates of well-recognised events such as changes in pre-dialysis weights, BPs, episodes of hyperkalaemia and details of medical interventions. Our strategy hence represents a pragmatic approach which also increases the study power when comparing selected (the routinely collected) parameters [61, 62] and ensures timely completion of the study provided there is appropriate matching of key confounding attributes [63].

To our knowledge, this is the first study exploring the views of patients receiving incremental HD through recognised qualitative research methods. Analysing patient experiences are an important aspect of gauging future demand for incremental HD and forms key part of the feasibility works conducted here. The qualitative methods in this study will also aid in achieving a deeper understanding behind some of the quantitative findings (e.g., dropout rates) making these findings much more informative.

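### Historical controls may date from any HD start since 2013 and are not matched on start date, so calendar period largely follows treatment arm in the descriptive safety comparison

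*Protocol article*

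**What the plan says.** The section on recruitment for the control arm defines the candidate pool: "All patients starting HD therapy since 2013, the inception date of the database, will be included in the searches". It gives no closing date and does not tie a control's start date to that of the matched participant.

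The Matching method section specifies a logistic propensity score "accounting for the following 14 variables: age, C-reactive protein (CRP), serum albumin, vascular access type, pre-dialysis serum creatinine, dialysis facility, body mass index (BMI"), and the list continues with "parathyroid hormone levels (PTH), diastolic blood pressure (BP), haemoglobin, systolic BP, vitamin K antagonist treatment, history of cardiovascular disease and antihypertensive treatment". Neither date nor year of HD start appears. Selection from the pool is then fixed: "Matching will take place using the nearest neighbour method (no pre-specified caliper range) with no replacements". The planned size is stated under Sample size: "The recruitment target is 20 participants in the active interventional arm and 40 in the historical control group (1:2 matching").

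The article gives no opening date for enrolment. It says that final analysis follows once the last participant "has completed 6 months follow-up (September 2021"). The Primary outcome section gives an 18-month recruitment period, and the Follow-up section gives 6 months from HD start.

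The Statement of novelty explains the purpose of the controls: "A control arm is needed to compare the rates of pre-defined safety events". It makes the use of historical controls conditional on adequate matching of the main confounders. The Secondary outcomes section lists the two-arm comparisons: BP, interdialytic weight gain, laboratory values, AEs and SAEs, hospitalisations, 4p-MACE, mortality and anaemia management. The Analysis section rules out formal tests on these but will look over the differences for possible signals.

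**The concern.** Calendar period is the confounder most specific to a historical control group, and the selection rule does not hold it constant. Given the same score, a 2013 starter is as eligible as a recent one. The 14 variables describe the patient at the start of dialysis. They cannot account for what changes after that point: how patients are managed, how ESA and IV iron are prescribed, or how events are written down. ESA and IV iron doses are themselves compared outcomes and follow the prescribing practice of the day. AEs are read largely from nursing narratives and so follow the documentation practice of the day.

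A difference between arms, or the absence of one, could therefore reflect period rather than regime. The comparison is meant to reveal signals, and the study's data are to shape the regime for a future RCT, so a misleading safety impression could carry forward.

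**Working it through.** **Check of the plan's own figures.** 20 participants × 2 = 40 controls, as stated. The listed score variables count to 14, as stated, with no calendar variable among them.

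**Participant start window (inferred).**
- Last start: September 2021 − 6 months' follow-up ≈ March 2021 (2021.2).
- First start: March 2021 − 18 months' recruitment ≈ September 2019 (2019.7).
- Midpoint: (2019.71 + 2021.21) / 2 = 2020.46.

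Consent can precede HD start, so actual starts may cluster towards the end of this window. That would widen the gaps below slightly.

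**Gap between arms.** Assume starts are evenly spread over time and the score is unrelated to date. Mean gap = participant midpoint − mean control start.

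| Control pool | Mean control start | Mean gap (years) | Share starting more than 3 years before midpoint |
|---|---|---|---|
| 2013.0 to 2019.71 | 2016.35 | 4.1 | (2017.46 − 2013.0) / 6.71 = 66% |
| 2013.0 to 2021.21 | 2017.10 | 3.4 | (2017.46 − 2013.0) / 8.21 = 54% |
| 2016.71 to 2019.71 (3 years before opening) | 2018.21 | 2.25 | not computed |

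The largest possible gap is 2021.21 − 2013.0 = 8.2 years with the pool as written, and 4.5 years with the 3-year pool.

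**What a drift would do.** The documents give no drift rate, so 2% to 5% a year in either direction is an assumption. The spurious rate ratio with no effect of the regime is (1 ± drift)^gap.
- Pool as written, gap 3.35 to 4.1 years. Rising rates: 1.02^3.35 = 1.07 up to 1.05^4.1 = 1.22. Falling rates: 0.98^3.35 = 0.93 down to 0.95^4.1 = 0.81.
- 3-year pool, gap 2.25 years. Rising: 1.05 to 1.12. Falling: 0.96 to 0.89.

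**Against chance.** The documents give no event rate. Assume a 6-month risk of 10% to 30%, that is 4 to 12 events among 40 controls. A 22% shift is then 0.9 to 2.6 events, against a Poisson standard deviation of √4 = 2.0 to √12 = 3.5.

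**The case against.** The strongest reply is that nothing the study decides on depends on this comparison. Feasibility is judged by acceptance and retention, and the controls enter neither. The two-arm comparison is secondary, descriptive and untested. Even the largest assumed drift moves event counts by less than their chance variation. That stands and limits the weight of the point, although continuous outcomes such as BP or drug doses may be more sensitive and are not quantified here.

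A reader might infer that calendar time is fully confounded with arm. The documents do not support that. The pool has no end date, and if it ran to March 2021, 1.5 / 8.21 = 18% of evenly spread starts would fall within the enrolment window.

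A reader might also infer that early database entries were poorer. The article says only that the database began in 2013. It also says that events are substantiated elsewhere in the electronic record, and one centre and one database serve both arms.

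The assumption that the score is unrelated to date is open to challenge too. Haemoglobin, PTH, BP, access type and facility are in the score, so any baseline drift in them would favour controls who resemble recent starters. This may shorten the true gap. It does not deal with changes in care or recording after HD start.

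It could be said that control for calendar period belongs in a statistical analysis plan. Detailed adjustment does, but the search window and matching rule are fixed in this article, and followed as written they leave period uncontrolled.

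**Conclusion.** The point holds as a limitation of the control-selection rule. As written, calendar period is largely, not wholly, aligned with arm. The mean gap is about 3.4 to 4.1 years, given evenly spread starts, a score unrelated to date, and a participant window inferred from the timeline.

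The 7% to 22% range for a spurious difference is illustrative. It rests on an assumed drift, and the documents establish neither that a drift exists nor which way it runs. It would be wrong to conclude that the safety comparison is biased by a known amount or that the feasibility conclusions are at risk. What follows is narrower: a safety signal, or its absence, could not be separated from a change over time without further information on when the controls started. The change is worth making but does not bear on the primary outcome.

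**What to change.** In the control-recruitment and Matching method sections, state that, where enough candidates exist, controls come from the most recent conventional-HD starters before the study opened. The preceding 3 years is one example. The window would be extended backwards as needed to keep match balance acceptable, with the balance criterion stated in advance.

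If the full 2013 pool is kept for the main match, re-run the same 1:2 matching within the recent window and present the two-arm safety tables for both matched sets. Re-matching is preferable to keeping only the recent members of the original 40. With an even spread to September 2019, that subset would be about 40 × 3 / 6.71 = 18 controls.

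In either case, report the distribution of HD start year among the controls.

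Adding start date to the propensity score is not advised, because it could separate the two groups almost completely.

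The cost is analysis time and one baseline row, with no new patients or data collection. The downside is a smaller pool. The article gives no yearly number of HD starts, so the loss of match quality cannot be judged in advance. Balance should therefore be shown for the restricted set. The gap is reduced, to about 2.25 years on the same assumptions, but not removed.
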